#### Exploratory Clinical Outcomes

We will measure and analyze specified, additional outcomes that are relevant to the diagnostic process. We will define diagnostic accuracy as having the correct diagnosis listed in the top 3 answers of the collective intelligence output (for intervention cases) or in the top 3 of the clinician’s list of possible diagnoses collected via survey data (for control cases). In addition, we will measure the number of diagnostic tests related to the initial complaint, ordered by the clinician within 30 and 90 days of the case presentation, and the number of unexpected visits (drop-in, urgent care, or emergency room) related to the initial presentation within 14 and 30 days of the index visit. Unexpected visits have been associated with higher risk of diagnostic error [1]. We refer to these as exploratory outcomes because we expect them to be highly variable both within and between clinicians and do not know whether we will have the statistical power to analyze them. Descriptive analyses of these outcomes may generate hypotheses for future study.

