### Study Objectives

In this pragmatic randomized controlled trial, we will examine the efficacy of a collective intelligence technology platform on improving primary clinicians’ confidence in their diagnostic assessments and their accuracy in making a correct diagnosis. We will also examine clinicians’ perceptions of the usability of the collective intelligence technology platform and their likelihood of using (ie *,* intention to use) such a platform in routine primary care or urgent care practice to assist with the diagnostic process.

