### Study Design

This is a pragmatic randomized controlled trial in which primary care clinicians are followed over 4 to 8 weeks to identify a minimum of 20 cases, for each clinician, with potential diagnostic uncertainty. Half of the selected cases for each clinician will be randomized to the intervention and the clinician will receive a collective intelligence output for those cases. Human Dx will generate collective intelligence for the remaining (control) cases, but clinicians will not receive the collective intelligence output for these cases (Figure 2).

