#### Exploratory Analyses

We will perform mixed-effect multivariable logistic regressions to compare diagnostic confidence, T2Dx, and diagnostic accuracy of intervention versus control cases, accounting for clustering by clinician and adjusted for baseline diagnostic uncertainty, perceived case difficulty, patient age, race, gender, number of comorbid conditions, type of visit (new, returning, drop-in, or urgent care), and primary care clinician characteristics such as professional degree (NP vs MD), specialty (family vs internal medicine), and years of experience. We have chosen covariates a-priori based on clinical judgment. For cases randomized to the intervention, mixed-effect bivariate logistic regressions will compare physicians’ diagnostic accuracy before and after reviewing the collective intelligence, adjusted for the aforementioned clinician characteristics. We will use bivariate and multivariable linear regressions to compare the number of diagnostic testing and use logistic regressions to compare the occurrence of unexpected clinical visits at 30 days between intervention versus control cases.

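### Exploratory diagnostic accuracy is scored on the platform's list in intervention cases and on the clinician's list in control cases, so the between-arm comparison cannot show whether clinicians became more accurate

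*Protocol article*

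**What the plan says.** All references are to the Protocol article.

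- **Aim.** Study Objectives asks whether the platform improves clinicians' "confidence in their diagnostic assessments and their accuracy in making a correct diagnosis". The Objective and Conclusions of the Abstract also name accuracy next to confidence.
- **Definition.** Exploratory Clinical Outcomes scores an intervention case as accurate by "having the correct diagnosis listed in the top 3 answers of the collective intelligence output (for intervention cases"). A control case is scored on the top 3 of the clinician's "list of possible diagnoses collected via survey data (for control cases").
- **Between-arm analysis.** Exploratory Analyses plans mixed-effect multivariable logistic regressions to "compare diagnostic confidence, T2Dx, and diagnostic accuracy of intervention versus control cases".
- **Within-arm analysis.** The same section plans, for intervention cases only, a comparison of physicians' "diagnostic accuracy before and after reviewing the collective intelligence, adjusted for the aforementioned clinician characteristics".
- **Timing.** Under Selection, Entry, and Randomization of Clinical Cases, a case is randomised only once its output is available. The output is produced in both arms; Study Design states that "Human Dx will generate collective intelligence for the remaining (control) cases". In control cases it is withheld from the clinician.
- **Data collected.** The same section on selection and randomisation has clinicians give an initial differential diagnosis for every case. In intervention cases, further questions after review ask how the output affected their diagnosis, plan and confidence.

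**The concern.** The objective concerns the clinician: does showing the output make the clinician more often right? The definition scores a different object in each arm. In an intervention case it scores the pooled list of outside contributors, and in a control case the treating clinician's list. An intervention case therefore counts as accurate even if the clinician disregarded a correct output. It counts as inaccurate if the clinician was right and the output was wrong.

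At stake is how the between-arm accuracy result will be read. It carries the name of an outcome in the stated aim and comes from the randomised comparison, so readers will take it as the effect of the intervention on clinicians. As defined, it is not that effect.

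**Working it through.** The plan gives no accuracy rate and no power figure for this outcome, so there is no figure to reproduce. The check is algebraic, followed by an illustration.

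**Step 1. What each arm contributes.** Let
- P = probability that the platform's top 3 contains the correct diagnosis,
- C = the same probability for an unaided clinician's top 3,
- A = the same probability for a clinician's top 3 after seeing the output.

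The plan scores P in intervention cases and C in control cases, so the planned contrast is P − C. The objective needs A − C. The output is fixed before allocation, so nothing the clinician does after allocation can alter the list scored in an intervention case. A does not appear in the planned contrast.

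**Step 2. Both directions of error (rates assumed).**

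| C | A | P | Effect on clinicians, A − C | Planned contrast, P − C |
|---|---|---|---|---|
| 0.60 | 0.60 | 0.75 | 0 | +0.15 |
| 0.60 | 0.65 | 0.75 | +0.05 | +0.15 |
| 0.60 | 0.70 | 0.60 | +0.10 | 0 |
| 0.60 | 0.70 | 0.55 | +0.10 | −0.05 |

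The contrast equals the effect on clinicians only when P = A.

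**Step 3. How often a null effect would look significant.** Set A = C = 0.60, so clinicians do not change. Sample Size Justification gives 660 cases, half in each arm, hence n = 330 per arm. Electronic Health Record Chart Review excludes cases still uncertain at 6 months but gives no expected number, so I also assume that half remain, n = 165.

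For a two-sided 0.05 test of two independent proportions, with p̄ = (P + C)/2:

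power = Φ{ [ (P − C) − 1.96·√(2p̄(1−p̄)/n) ] / √[ (C(1−C) + P(1−P))/n ] }

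For P = 0.70 and n = 330: p̄ = 0.65; √(0.455/330) = 0.0371; 1.96 × 0.0371 = 0.0728; √(0.45/330) = 0.0369; (0.10 − 0.0728)/0.0369 = 0.74; Φ(0.74) = 0.77.

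| P (C = A = 0.60) | Apparent gain | n = 330 per arm | n = 165 per arm |
|---|---|---|---|
| 0.65 | +0.05 | 0.26 | 0.15 |
| 0.70 | +0.10 | 0.77 | 0.48 |
| 0.75 | +0.15 | 0.99 | 0.83 |

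With C = 0.50 and the same three steps up to P, the values at n = 330 are 0.25, 0.73 and 0.98. With C = 0.70 they are 0.30, 0.85 and above 0.99. Clustering is ignored: the r = .3 in the plan refers to confidence ratings, and the plan gives no value for accuracy.

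**Step 4. Consistency within the plan.** The before/after analysis needs a clinician-level accuracy score in intervention cases. The definition in Exploratory Clinical Outcomes supplies only a platform-level score there. One outcome name thus covers two different measures.

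**The case against.** The strongest reply is that this outcome is exploratory. The plan says it may lack power for these outcomes and that descriptive results may only generate hypotheses. Multiple Hypothesis Testing repeats the hypothesis-generating status, and the Discussion leaves the impact on accuracy to larger work. This stands as a limit on the consequence. It does not remove the defect, because the exploratory label deals with power and multiplicity, not with which list is scored.

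A second reply is that the plan already scores clinicians, by comparing "diagnostic accuracy before and after reviewing the collective intelligence" in intervention cases. This also stands in part. Participants are told to record their initial thinking before opening the output, so the analysis bears directly on the aim. But it is confined to one arm and has no randomised control, so it mitigates the flaw without repairing the between-arm comparison.

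A third reply is that platform versus unaided clinician is a fair question. It is, but it is not the stated one. It also does not need randomisation, because the output and the clinician's initial list are both planned for every case.

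A reader might further infer that the reference diagnosis is contaminated, since it comes from a chart that the output may have influenced in intervention cases. The documents do not establish this. Two investigators review each record independently and settle differences by consensus, and nothing in the plan allows any influence to be sized. Scoring the clinician's list in both arms would rely on the same chart, so the point is separate and is not pressed here.

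**Conclusion.** The definition is wrong as written for the use the plan makes of it. The between-arm accuracy comparison estimates P − C, is insensitive to whether clinicians used the output, and cannot support the aim of improving "their accuracy in making a correct diagnosis". This follows from the definition and from the timing of randomisation, and needs no assumed rates.

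The probabilities (about 0.77 or 0.99 at 330 per arm, 0.48 or 0.83 at 165) are illustrative only. They rest on assumed accuracy rates, independent cases and, for the lower pair, an assumed loss of half the cases.

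Two stronger readings are not supported. The first is that the trial's main results are compromised: the primary outcome (diagnostic confidence) and the secondary outcome (time to diagnosis) do not use this definition. The second is that the plan offers no evidence at all on clinician accuracy: the before/after analysis offers some, though uncontrolled.

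**What to change.** - Define accuracy in both arms as the adjudicated final diagnosis being in the clinician's own top 3. Use the post-review list in intervention cases and the questionnaire list in control cases. The between-arm contrast then becomes A − C, which is zero when clinicians do not change.
- Reconcile Exploratory Clinical Outcomes with Exploratory Analyses, so that the between-arm and before/after analyses use the same clinician-level measure.
- Report the platform's own top-3 accuracy as a separate outcome, compared with the clinician's list within control cases, where the output exists but the clinician did not see it.
- If the questionnaire did not collect a post-review list, relabel the between-arm comparison as platform versus unaided clinician and draw no conclusion from it about improved clinician accuracy.

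**Cost.** Rewording, provided the post-review list exists. The before/after analysis presupposes some post-review diagnosis, but the questionnaire appendix is not shown, so a full revised top 3 cannot be confirmed. Results states that data collection was complete as of June 2019, so a missing list could not be recovered by rewording and the relabelling would apply. Control-case outputs are already generated under the plan, and no sample-size figure changes.

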Once the collective intelligence output becomes available for a case, the study team randomizes it to the intervention or control cases. The study team assigned each case a unique study identification number for tracking purposes. Using a random number generator in blocks of four, we will randomize half of the cases, for each clinician, to an intervention group in which the clinician will receive a collective intelligence output between 60 and 80 hours from the time the clinician saw the patient in the clinic (ie, within 24-36 hours of case entry). For cases randomized to the controlled group, Human Dx will generate collective intelligence, but it will not be shared with the clinician. Clinicians will complete an online postvisit questionnaire for all of their cases (control and intervention) that provides their initial impressions of the case (eg, differential diagnosis and perceived case difficulty) and level of diagnostic confidence. The questionnaire for cases assigned to the intervention group includes additional questions that the clinician will answer after reviewing the collective intelligence output to assess the effect of the output on their diagnosis, plan, and confidence. The study scribes and the *contributors* on Human Dx will be blinded to case randomization.

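### Diagnostic accuracy is scored on the platform's list in one arm and the clinician's list in the other, leaving the control-case outputs unused and forgoing a within-case comparison

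*Protocol article*

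**What the plan says.** Under Exploratory Clinical Outcomes, the Protocol article counts an intervention case as accurate on the basis of "having the correct diagnosis listed in the top 3 answers of the collective intelligence output (for intervention cases". A control case is judged on the clinician's "list of possible diagnoses collected via survey data (for control cases". Exploratory Analyses then uses mixed-effect logistic regression to "compare diagnostic confidence, T2Dx, and diagnostic accuracy of intervention versus control cases".

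Both lists exist in both arms:

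- Study Design states that "Human Dx will generate collective intelligence for the remaining (control) cases, but clinicians will not receive the collective intelligence output for these cases". Selection, Entry, and Randomization of Clinical Cases adds that a case is randomized only once its output is available, so every randomized case has one.
- The same section states: "Clinicians will complete an online postvisit questionnaire for all of their cases (control and intervention) that provides their initial impressions of the case". The differential diagnosis is among those impressions.
- The chart review section applies one adjudication of the final diagnosis, at 6 months, to all cases.

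One further accuracy analysis is planned, in intervention cases only. It concerns physicians' "diagnostic accuracy before and after reviewing the collective intelligence, adjusted for the aforementioned clinician characteristics". The authors class accuracy as exploratory and say of these outcomes that they "do not know whether we will have the statistical power to analyze them".

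**The concern.** The scoring rule makes the planned accuracy contrast a comparison of the platform with the unaided clinician, each judged on a different set of cases. The article already holds both lists on the same cases, so each case could serve as its own control. An outcome whose power is admittedly unknown is thus given a less precise analysis than the data allow, and platform outputs built from at least 5 contributors per control case go unscored.

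There is also a validity point. The final diagnosis is adjudicated from the medical record, to which the treating clinician contributes. In intervention cases the clinician has been sent the output, so the output may influence the standard against which it is judged. In control cases this cannot happen, yet those are the cases where the platform is not scored.

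**Working it through.** **1. Which lists exist and which are scored**

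| | Platform output | Clinician's initial list |
|---|---|---|
| Intervention cases | exists; scored in the between-arm contrast | exists; scored only in the before-after analysis |
| Control cases | exists; not scored in any described analysis | exists; scored in the between-arm contrast |

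**2. Inputs**

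- From Sample Size Justification: 33 clinicians × 20 cases = 660 cases, 330 per arm. This was set for diagnostic confidence. No baseline rate is given, so it cannot be reproduced uniquely. One set that returns it is 55% versus 75%, two-sided 5%, 80% power: 89 per arm × (1 + 9 × 0.3) = 89 × 3.7 = 329 per arm, or 32.9 clinicians. The article gives no variance or power for accuracy, so only the 330 per arm is carried forward.
- Assumed: clinician top-3 accuracy 50%, platform 50% or 70%.
- Assumed: within-case correlation ρ between the two lists being correct, 0 to 0.5. The article gives none.

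**3. Variances with no clinician-specific difference**

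With v = p(1 − p) for platform (P) and clinician (C):

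- Unpaired, as planned: (vP + vC)/330.
- Paired: (vP + vC − 2ρ√(vP·vC))/n, with n = 330 (control cases) or 660 (all cases).

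The unpaired SE is √(0.50/330) = 0.039 at 50% versus 50% and √(0.46/330) = 0.037 at 70% versus 50%. With equal variances, the ratio of unpaired to paired variance is 1/(1 − ρ) on 330 cases and 2/(1 − ρ) on 660.

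| ρ | SE, 330 control cases | Ratio | SE, all 660 cases | Ratio |
|---|---|---|---|---|
| 0 | 0.037–0.039 | 1.0 | 0.026–0.028 | 2.0 |
| 0.25 | 0.032–0.034 | 1.33 | 0.023–0.024 | 2.67 |
| 0.5 | 0.026–0.028 | 2.0 | 0.019 | 4.0 |

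On all cases, the factor of 2 comes from using 660 cases rather than 330 per list; the rest comes from pairing. At ρ = 0.6 the all-case ratio would be 5.0. At ρ = −0.1 it would be 1.82, and the control-only ratio would be 0.91. Excluding unresolved cases equally from both arms leaves the ratios unchanged.

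**4. If clinicians differ in accuracy and the platform does not share that difference**

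Scale each variance to 1 and let τ be the ICC of clinician accuracy, with ρ now the case-level correlation that remains:

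- Unpaired: τ/33 + (2 − τ)/330.
- Paired: τ/33 + (2 − τ − 2ρ√(1 − τ))/n.

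At τ = 0.3, borrowed from the article's r for confidence ratings:

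- Unpaired: 0.00909 + 0.00515 = 0.01424.
- All 660, ρ = 0: 0.00909 + 0.00258 = 0.01167, ratio 1.22.
- All 660, ρ = 0.5: 0.00909 + 0.00131 = 0.01040, ratio 1.37.
- 330 control cases, ρ = 0: ratio 1.00.
- 330 control cases, ρ = 0.5: 0.00909 + 0.00262 = 0.01171, ratio 1.22.

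For ρ from 0 to 0.5 on all cases, τ = 0.05 gives 1.66 to 2.48 and τ = 0.1 gives 1.49 to 1.97. If the clinician effect is shared by both lists, it cancels and the ratios in step 3 return.

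**The case against.** The strongest objection is that this improves the answer to a question the trial does not pose. Study Objectives asks whether the platform improves clinicians' own accuracy, and no section states a platform-versus-unaided-clinician objective. The larger weakness of the definition is that the arms are scored on different objects, and pairing does not cure that. This stands, so the paired analysis must be kept separate. It does not dispose of the point: the article fixes this contrast explicitly, and repairing the clinician comparison would still leave the control outputs unscored.

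Several limits on size also stand:

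- A reader might infer that the plan costs two to four times the variance outright. That needs ρ between 0 and 0.5, cancelling clinician differences and sound initial lists in intervention cases. The article establishes none of these.
- The planned regression adjusts for perceived difficulty, comorbidity, visit type and other covariates. The crude unpaired SE may therefore overstate the gap, by an amount that cannot be computed.
- Under Postvisit Questionnaires, intervention clinicians receive the output link in the same email as the questionnaire. Their initial lists count as unaided only if they follow the instruction to answer first.
- A reader might infer that half of each list is never used. That is true of the between-arm contrast only, since the before-after analysis also scores clinicians' lists in intervention cases.

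Finally, accuracy is exploratory and the primary and secondary outcomes are untouched. A condensed article need not list every exploratory analysis, but here it states a scoring rule, and that rule is what excludes the control outputs.

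**Conclusion.** The point holds as a low-cost gain in precision and validity for an exploratory outcome. The definition leaves the control outputs unused and makes the accuracy contrast an unpaired comparison of platform with unaided clinician, although both lists are held for every case.

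For ρ of 0 to 0.5, the variance gain from pairing is about 1 to 2 times on the 330 control cases and about 2 to 4 times on all 660, if clinician differences cancel. With an unshared ICC of 0.3 for clinician accuracy, it is about 1.2 to 1.4 times on all cases and 1.0 to 1.2 times on control cases alone. That ICC is stated for confidence, so its use for accuracy is an assumption. The validity gain from control cases, where the output was never seen, does not depend on ρ.

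Two stronger readings are not supported. Omitting pairing does not by itself bias the randomized contrast. Nor would the paired analysis show whether access to the output makes clinicians more accurate.

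**What to change.** Amend Exploratory Clinical Outcomes and Exploratory Analyses as follows:

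1. Score both the platform's top 3 and the clinician's initial top 3 in every case with an adjudicated final diagnosis, in both arms.
2. Analyse platform versus unaided clinician as a paired within-case difference in proportion correct, with standard errors clustered by clinician.
3. Make the control cases the main set, because the clinician never saw the output there. Report all cases as a supporting analysis, and note that in intervention cases the output link came in the same email as the questionnaire.
4. Label the analysis exploratory. Keep it separate from the between-arm analysis of the output's effect on clinicians' own accuracy, which it does not answer.

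The cost is a wording change and a little more scoring: stored control outputs must be matched to final diagnoses that are adjudicated anyway. The before-after analysis already requires the initial lists in intervention cases to be scored. No new patients or data collection are needed.

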#### Satisfaction and Usability

We will use the exit survey and interview described above to assess the usability of collective intelligence to assist clinicians’ diagnostic process in routine primary care and urgent care cases and examine their willingness to use collective intelligence in practice. Through the survey, we will determine the Net Promoter Score (NPS) as a quantitative measure of user satisfaction and willingness to use and a modified TAM score (overall and for each theoretical variable) as a quantitative measure of usability. The NPS is based on a single question: “How likely is it that you would recommend our service to a friend or colleague?” This score is increasingly used in health services research as a summary of consumer satisfaction [20]. The theoretical variables comprising the TAM score include PU, PEU, Trust, perceived facilitators, and intention to use.

